## Abstract

**Introduction:**

The enteric microbiota drives inflammation in Crohn’s disease. Yet, there are no placebo controlled trials evaluating the efficacy and safety of faecal microbiota transplantation (FMT) in inducing and maintaining remission in patients with active Crohn’s disease. The Microbial Restoration (MIRO) study aims to establish this evidence.

**Methods and analysis:**

At two specialist inflammatory bowel disease centres, 120 enrolled patients will have a 3-week period of diet optimisation (removal of ultra-processed foods) together with a 7-day course of antibiotics (to facilitate subsequent FMT engraftment). Patients will then be stratified to upper gut (for disease proximal to the splenic flexure) or lower gut (distal to the splenic flexure) disease. Patients will then be randomised in a 2:1 ratio to receive anaerobically prepared stool or placebo for 8 weeks either by gastroscopy, or colonoscopy and enemas. Clinical response at 8 weeks (Crohn’s Disease Activity Index (CDAI) reduction ≥100 points or to <150 points) is the primary outcome measure. Non-responders to placebo and partial responders to FMT (CDAI decrease <100 but >70) receive FMT for weeks 8–16.

Patients achieving clinical response from FMT after 8 or 16 weeks will be randomised in a 1:1 ratio to either a 44-week maintenance phase of FMT or placebo. Patients will receive FMT from one donor throughout the study.

The MIRO study will establish whether FMT is an effective and safe therapy to induce and maintain remission in patients with active Crohn’s disease.

**Ethics and dissemination:**

Ethical approval has been received by the St Vincent’s Hospital Melbourne Human Research Ethics Committee (HREC-A 084/21). The results will be disseminated in peer-reviewed journals and presented at international conferences.

**Trial registration number:**

ClinicalTrials.gov: NCT04970446; Registered on 20 July 2021.

STRENGTHS AND LIMITATIONS OF THIS STUDYThis is a randomised placebo-controlled study, providing the highest level of evidence about both efficacy and safety of faecal microbiota transplantation (FMT) in Crohn’s disease for the induction and maintenance of remission.The optimisation phase of diet and antibiotics is postulated to enhance FMT engraftment.The scientific analyses will determine organisms, and metabolic pathways, associated with response or lack of response to FMT.Confining the study to two tertiary centres will ensure robust compliance with the study protocol, while the diverse patient population ensures generalisability.The use of the Crohn’s Disease Activity Index as the primary endpoint, while providing a standard means for establishing comparability with other studies, is inherently largely subjective and therefore potentially unreliable.

## Introduction

### Background and rationale

 Crohn’s disease inflammation is believed to be driven by a perturbed microbiota, influenced by genetic and environmental risk factors.^1^,^3^ Luminal and mucosa-associated Crohn’s disease microbiota profiles are distinctly different from healthy controls and patients with ulcerative colitis (UC).^1^,^8^

Considering the central role of a disturbed microbiota in inflammatory bowel diseases (IBD), faecal microbiota transplantation (FMT) has been postulated to shift the microbiota into a healthy, well-balanced community of organisms, thereby correcting the proinflammatory milieu. Consequently, randomised controlled trials have established the efficacy of FMT in achieving and maintaining remission in active UC.^9^,^18^

A strong motivation for exploring the therapeutic value and safety of FMT in Crohn’s disease relates to the benefits and risks of traditional immunosuppressive therapies, which are associated with clinical response rates of less than 50% by week 12, diminishing response over time,^19 20^ and significant risks.^21^

FMT has shown promising efficacy in Crohn’s disease cohort studies. However, only two randomised controlled trials have been published, with only one including a placebo control group.^22^,^24^ Sokol *et al* performed a small multicentre randomised, single-blind placebo-controlled trial in France (n=17), evaluating the efficacy of a single FMT following clinical remission induced by corticosteroids. Of 17 patients with mainly ileocolonic disease, 8 patients received single donor, fresh stool via colonoscopy and 9 patients received Sham FMT. Corticosteroid-free remission was seen in 88% of the FMT arm versus 44% sham FMT at week 10 (not statistically significant). Endoscopic disease activity (Crohn's Disease Endoscopic Index of Severity) significantly declined by week 6 following FMT (8.5 [4.6; 13.0] vs 3.5 [1.0; 8.9], p=0.03) but not sham treatment (2.4 [0.0; 8.3] vs 2.7 [0.7; 10.0]; p=0.8).^23^

The nature of faecal transplantation used may have bearing on its effectiveness. Whole stool that is anaerobically processed preserves bacterial populations compared with preparation in ambient air.^25^,^27^ The latter is not necessary to achieve cure in *Clostridioides difficile* infection, but may be critical in Crohn’s disease, in which there is a reduced abundance of butyrate-producing oxygen-sensitive organisms.^28^ This Microbial Restoration (MIRO) study will use anaerobically prepared stool.

In the MIRO study, an ‘optimisation’ phase is designed to improve microbial engraftment. In this randomised, double-blind, placebo-controlled trial, the cohort will be stratified into two groups according to disease phenotype to determine route, dose and frequency of FMT administration. Randomisation will be 2:1 for the active intervention group versus control in the induction phase, followed by re-randomisation at 1:1 for the maintenance phase. The study protocol adheres to the Standard Protocol Items: Recommendations for Interventional Trials statement (2013) (online supplemental file 1).

### Objective

This study aims to investigate the efficacy and safety of FMT in inducing and maintaining remission in Crohn’s disease.

## Methods and analysis

### Study setting

Patient diversity will be ensured by the recruitment process. The study will be conducted at two Australian secondary and tertiary specialist IBD centres that serve large and diverse catchment areas. Patients will be referred by gastroenterologists from within, and outside of, these two specialist centres, including from both private practices and public clinics across two Australian states. Study was started in May 2022 with intended conclusion in April 2026.

### Recipient eligibility: induction phase

#### Inclusion criteria

Participants aged 18–70 years with Crohn’s disease proven by endoscopic, histological and/or radiological assessment.Confirmed endoscopic active inflammation (unless isolated small bowel disease that is inaccessible by endoscopy, in which case sonographic inflammation is sufficient) within 6 months of study entry.Crohn’s Disease Activity Index (CDAI) Score of 220–450.At least one of the following:C-reactive protein (CRP)≥5 mg/L.Faecal calprotectin≥100 µg/g.Inflammation on imaging (either intestinal ultrasound (IUS) or Magnetic Resonance Imaging (MRI).Willing and able to attend the study sites for regular endoscopic procedures.

#### Exclusion criteria

Exclusion criteria include active perianal or fistulising disease; pregnant or intending to become pregnant within 12 months; enteropathy or colitis other than Crohn’s disease; symptomatic intestinal stricture likely to require surgical or endoscopic treatment; presence of a stoma; presence of an ileoanal pouch; total white cell count less than 3.0×10^9^/L; albumin less than 20 g/L; immunodeficiency (beyond that caused by immunosuppressants used for the treatment of IBD) for example, HIV or common variable immune deficiency; anaphylaxis/severe allergy to food; thiopurine, methotrexate or biologic agent whose dose has been modified within the past 2 months; small molecule inhibitors whose dose has been modified within 1 month; aminosalicylates use within 2 weeks of study entry; prebiotic, probiotic or antibiotic therapy, or over-the-counter supplement therapy in the 2 weeks prior to study entry; rectal topical Crohn’s disease therapy in the 2 weeks prior to study entry; prednisolone dose >20 mg or budesonide dose >6 mg; unwilling or unable to taper corticosteroids to zero within 8 weeks of initial FMT; active gastrointestinal infection; alcohol consumption of a dependent nature; primary sclerosing cholangitis; any condition that the treating gastroenterologist deems to pose a theoretical risk to the patient undertaking FMT; any patient that the treating clinicians feel is incapable of participating in the safe use of FMT.

### Recipient eligibility: maintenance phase

#### Inclusion criteria

Patients who have had a clinical response (CDAI decrease of ≥100 points or CDAI <150 points) to blinded FMT therapy at week 8, or to open-label FMT at week 16, can enter the maintenance study.

### Donor eligibility

#### Donor inclusion and exclusion criteria

Healthy people aged 16–60 years old who reside within the metropolitan area of the collection centre with a body mass index between 18.5 and 25. Extensive medical history and investigations must exclude the presence of any active gastrointestinal symptoms, medical or psychiatric comorbidities, infectious diseases or antibiotic-resistant bacterial colonisation. Donors must be non-smokers and not use medications, alcohol or recreational drugs.

The donor inclusion and exclusion criteria are defined by the stool bank, BiomeBank, under the jurisdiction of the Australian Therapeutic Goods Administration (TGA). The inclusion and exclusion criteria are regularly examined and amended by a team of gastroenterologists and infectious diseases physicians to reflect the current relevant risks to the population.

### Screening processes

#### Participant screening

Referred patients will be assessed by the trial team for eligibility by an initial phone screen evaluating recent endoscopy results, faecal (calprotectin) and serum (CRP) disease activity biomarkers and relevant imaging. The CDAI Score will be calculated, and medical history taken to identify exclusion criteria. Patients who satisfy eligibility criteria will then be invited to the trial hospital sites for a screening visit.

At the study centre screening visit, an extensive medical history will be taken by a physician and clinical nurse. Venepuncture for routine pathology and infections, and a stool assessment for infectious pathogens, antibiotic-resistant bacteria and faecal calprotectin, is undertaken. An IUS is performed to evaluate the presence of sonographic inflammation (defined by a combination of bowel wall thickness ≥3 mm and hyperaemia (Limberg score ≥2). If the location of disease is inaccessible on IUS, or the views are suboptimal, an MRI scan of the small and large bowel is performed. The same modality of imaging will be conducted for the duration of the trial.

#### Donor screening

The screening assessment involves specialised history taking to identify comorbidities and a family history of medical conditions. Respiratory, blood and stool specimens are obtained to identify medical conditions, chronic infections and colonisation with antibiotic-resistant bacteria.

If the donor meets eligibility, the stool is quarantined for 3 months. The donor is reassessed at 3 months; if re-evaluation is negative, then stool can then be used and the donor qualifies for ongoing donation.

### Randomisation and stratification

Eligible patients will be stratified according to their historical maximal extent of intestinal involvement. Patients with intestinal disease proximal to the splenic flexure will be assigned upper gastrointestinal delivery of therapy. Patients with disease distal to the splenic flexure, or an ileorectal or ileosigmoid anastomosis, will receive lower gastrointestinal delivery.

There will be a total of four randomisation tables. Each table will represent stratification according to the assignment to upper or lower gastrointestinal delivery, and the phases of the study (induction or maintenance). Randomisation within these tables is computer generated by a statistician and then uploaded to a web-based platform.

For the induction phase, patients are randomised to FMT therapy or placebo in fixed block sizes of three patients in a ratio of 2:1, respectively. Re-randomisation occurs for participants entering the maintenance phase, from either the induction or open-label extension phases, in blocks of two in a ratio of 1:1.

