### Preservation of double blinding

The participants, clinicians, research team and outcome assessors will be blinded to treatment allocation. The placebo product, packaging and labelling will be identical in appearance to the FMT product. The barcode numbers are indistinguishable between placebo and FMT products. The placebo product is frozen, stored and handled identically to the FMT product at each hospital site to prevent unblinding of study investigators during retrieval.

Unblinding will take place the day prior to the week 8 assessment of the induction phase to allow preparation of FMT or placebo for the open-label phase as FMT or placebo endoscopic infusion requires 4 hours of thawing. This unblinding will be undertaken by a designated team member who is not involved in the clinical running of the trial; they will allocate the maintenance syringe kit number. The study assessment, including IUS and endoscopy, will be performed by a study member who remains blinded to the treatment arm. In the event that a patient needs to be unblinded for medical care, a 24-hour contact number is available for immediate unblinding.

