Other practical considerations regarding the route of administration include tolerability and safety. There will be several protocolised measures to mitigate the rare but significant risk of aspiration pneumonia with gastroscopic delivery, including performing the procedure with the patient reclining at 45°, the use of a paediatric colonoscope for administration directly into the distal duodenum/jejunum, low FMT volume (100 mL), intraprocedural intravenous metoclopramide and postprocedure recovery in the upright position.

The FMT doses are based on prior FMT in UC studies,^9 18^ as well as the two randomised controlled trials conducted in Crohn’s disease to date.^23 24^ Additionally, systematic reviews evaluating the dose of FMT in *Clostridioides difficile* infection revealed that multiple FMT is more effective than single FMT and that the reduced efficacy of a dose<50 g of stool has been compensated for with the increased cumulative dose of multiple administrations.^42 43^

The use of a clinical score for entry and as the primary endpoint is consistent with the current clinical trial standards for Crohn’s disease, according to US Food and Drug Administration clinical trials guidelines (ref website: https://www.fda.gov/regulatory-information/search-fda-guidance-documents/crohns-disease-developing-drugs-treatment). However, the lack of objectivity of this endpoint makes it challenging to interpret in certain settings. Extensive additional clinical, biochemical, sonographic and endoscopic data will be collected to provide objective assessment of disease activity, reflecting the recent shift towards objective assessment of therapeutic interventions.

For ethical reasons, an open-label extension allows initial placebo-treated patients to access FMT, and patients’ Crohn’s disease medications are continued at a stable dose.

An open-label FMT induction extension requires unblinding of patients at week eight to determine the next phase of trial progression. To maintain blinding throughout the maintenance phase of the trial, patients are re-randomised on entry into this phase.

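### Published fixed blocks of three, with each patient's arm disclosed at week 8, let well-placed staff deduce up to 44% of induction allocations before the week-8 CDAI is scored

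*Protocol article*

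**What the plan says.** All references are to the protocol article.

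- **Blocks (Randomisation and stratification).** In induction, "patients are randomised to FMT therapy or placebo in fixed block sizes of three patients in a ratio of 2:1, respectively".
- **Lists (same section).** There are four: "Each table will represent stratification according to the assignment to upper or lower gastrointestinal delivery, and the phases of the study (induction or maintenance"). Two of them serve induction. Centre is not named as a factor, although "The study will be conducted at two Australian secondary and tertiary specialist IBD centres" (Study setting).
- **Disclosure at week 8 (Discussion).** "An open-label FMT induction extension requires unblinding of patients at week eight to determine the next phase of trial progression".
- **Next phase by arm (Induction phase).** FMT responders enter maintenance and placebo responders leave. Placebo patients are offered open-label FMT, as are FMT partial responders. Other FMT non-responders have no onward route.
- **Code break (Preservation of double blinding).** "Unblinding will take place the day prior to the week 8 assessment of the induction phase", because product needs four hours to thaw. The section names who does it: "This unblinding will be undertaken by a designated team member who is not involved in the clinical running of the trial". On kits for the next phase, it says of the same person that "they will allocate the maintenance syringe kit number". The section adds that the week-8 assessment is made by someone still blinded.
- **Endpoint.** The primary endpoint is clinical response by CDAI at week 8. The strengths and limitations box says the CDAI "is inherently largely subjective and therefore potentially unreliable".

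**The concern.** With one placebo slot in every three, and both block size and ratio in print, a block gives itself away quickly. If a block's placebo patient is known, everyone after that patient is on FMT. If two FMT patients are known, the third is on placebo. Because disclosure happens patient by patient at week 8, later members of the block may still be in blinded treatment when their arm becomes inferable.

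The stake is the primary endpoint. A person who can infer the arm, and who records or influences any part of a subjective score, can shift the response rate in a trial that reports blinding of participants, clinicians, research team and assessors. Nobody need break the code improperly.

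**Working it through.** **The plan's own figure.** The protocol gives no figure for predictability. Its sample size, used in step 5, reproduces. With 30% v 60%, 2:1, two-sided 0.05, 80% power and pooled rate (0.3 + 2×0.6)/3 = 0.5, the placebo group needs [1.96√(1.5×0.25) + 0.842√(0.21 + 0.24/2)]²/0.3² = 31.5, so 32. Then 32 + 64 = 96, and 96/0.8 = 120.

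**1. Ceiling.** The three orders are equally likely. An allocation is certain when earlier block members leave only one possible arm.

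| Order | Certain allocations | Number |
|---|---|---|
| P F F | 2nd (F), 3rd (F) | 2 |
| F P F | 3rd (F) | 1 |
| F F P | 3rd (P) | 1 |

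Total 4 of 9 = 44.4%. Three of the nine are certain FMT and one is certain placebo.

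**2. Guessing.** With full block knowledge, the best guess is right with probability 2/3, 2/3 and 1 at positions 1, 2 and 3: mean 7/9 = 77.8%. Always guessing FMT is right 66.7% of the time.

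**3. Partial knowledge.** If each earlier block member's arm is known with probability q, and block positions are known, three of the four certain cases need one known block-mate (q each) and the F F P case needs two (q²). The share is (3q + q²)/9.

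- q = 1: 4/9 = 44%
- q = 0.7 (a centre with 70% of patients, own patients only): 2.59/9 = 29%
- q = 0.5 (even split): 1.75/9 = 19%
- q = 0.3 (the smaller centre in a 70:30 split): 0.99/9 = 11%

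The centre split is an assumption; the protocol gives none. Attrition acts the same way: if 20% left without disclosure, q = 0.8 gives 3.04/9 = 34%.

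**4. Timing.** Week 8 is a fixed interval from the start of treatment, so earlier block members normally reach it first. Simulated visit shifts of ±1 week leave the ceiling at 44 to 45%. Deduction before a patient's own randomisation is a different matter. The May 2022 to April 2026 calendar is about 208 weeks; less 60 weeks of follow-up and 3 of optimisation, about 145 remain for accrual. Simulating 120 patients over 100 to 145 weeks, with 50 to 70% in the larger stratum, gives about 1 to 3% overall (up to about 9% within a stratum holding 30%).

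**5. What exclusion would leave.** From the table, the allocations that are not certain number 5 of 9: three FMT and two placebo. Of 96 completers, 96×5/9 ≈ 53: 96×3/9 = 32 FMT and 96×2/9 ≈ 21 placebo. At 60% v 30%, the pooled standard error is 0.140 and the unpooled 0.132, so power is Φ[(0.30 − 1.96×0.140)/0.132] ≈ 57% (about 62% with the unpooled error throughout).

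**The case against.** The case for the plan has real weight.

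- **Safeguards exist.** The person breaking the code stands outside the clinical running of the trial, and the assessor is blinded. This stands for the current patient's code. It does not reach inference from block-mates whose arms are already open.
- **44% needs unusual knowledge.** The lists are computer generated and held on a web platform, and nothing says that site staff see block order or the other centre's allocations. This stands, and is why 44% is a ceiling.
- **The pathway alone does not always show the arm.** Only direct entry to maintenance does so. Exit and open-label treatment each cover both arms until read with the CDAI change, and a partial responder given open-label FMT stays ambiguous. This stands, but the Discussion says patients are unblinded at week 8 in any case.
- **Staff influence is limited.** Patient-reported outcomes pass from the app straight to the database, and the corticosteroid taper follows set steps. This narrows the route to bias. It does not protect items recorded at the visit, and patients are not shown to know block positions.

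Three stronger readings are tempting but unsupported. First, the day-before code break does not contribute to the 44%: if it leaked, every allocation would be exposed; if the safeguards hold, it adds none. Second, the maintenance blocks of two do not carry the same risk, because patients and study team stay blinded at week 52 or 60, so there is no routine disclosure. Third, selection of patients at entry is not seriously exposed, given the small pre-randomisation share in step 4.

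**Conclusion.** The weakness is real but conditional. Fixed, published blocks of three combined with patient-by-patient disclosure at week 8 make up to 44% of induction allocations certain before the primary CDAI is scored. This assumes an observer who knows block order and every earlier allocation in the list. With one centre's allocations and known positions, the figure is about 19 to 29% for a centre recruiting half to 70% of patients; it is lower for a smaller centre or where positions are unknown. The stated blinding safeguards do not close this route.

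The timing of the code break is a separate and lesser risk, mitigated by the independent unblinder and blinded assessor. What remains is that the document states no requirement to fix the CDAI before the code is broken.

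Nothing here shows that bias has occurred or that the trial cannot answer its question. The point deserves correction because the endpoint is subjective and the remedy is inexpensive.

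**What to change.** 1. **Unused part of the two induction lists:** use randomly varying block sizes, for example 3, 6 and 9, known only to the statistician. Merely moving to a fixed block of six would still leave 28.9% deducible if its size were known. If randomisation is already complete, this step no longer helps.
2. **Week-8 CDAI:** record and lock it, both app diary and visit items, before the arm or the next phase is disclosed to anyone except the designated unblinder. That person may still prepare product in advance, so the thawing schedule is unaffected.
3. **Patients already randomised:** pre-specify a sensitivity analysis excluding those whose arm was deducible from block position. The exclusion depends on the list and not on outcome. It leaves about 53 of 96 completers (about 32 FMT v 21 placebo), so present it as a supportive check only.

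Cost: a regenerated list, possible slight imbalance at the end of a stratum, one lock step per patient, and one low-powered extra analysis.
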